#### Randomization and allocation

The study is a blinded, randomized, controlled trial. Before baseline assessments, participants are randomly assigned to one of the three groups: a group that performs the planned physical exercise program based on daily heart rate variability (HRVG), a group that performs the conventional pre-planned physical exercise program (PEG) and a control group (CG).

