### Participants

#### Recruitment and eligibility

A total of 90 patients are being recruited from the Oncology Service of Cantabria, concretely, they are being enrolled in the University Hospital of Marqués de Valdecilla. The enrolment consists of two phases. First, an oncologist and a radiologist select patients who fulfill the following inclusion criteria: (a) women aged between 18 and 65 years, (b) having luminal or triple-negative breast cancer, (c) having received and finished chemotherapy and radiotherapy treatment. In addition, patients are excluded if: (a) they have been scheduled for surgery during the study (b) they have HER2 + breast cancer, (c) they have severe heart disease before chemotherapy, (d) they have finished the cancer treatment more than 5 months ago, (e) they have metastatic cancer, (f) they have any injury which prevents them to perform the intervention or the evaluation correctly, (g) they have severe psychiatric illnesses.

In the second phase, patients are called to the hospital by the oncologist and the physical exercise professional to explain in detail the study and each intervention group requirement. After answering patients’ questions and asking for some technical needs for mobile phone application licenses, a complete description of the study is given to the participants.

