### Interventions

#### Physical exercise programs

First, the common aspects between the two exercise groups are going to be mentioned, to explain afterwards the peculiarities of each physical exercise program. The programs of both experimental groups, PEG and HRVG, will last 14 weeks, and patients will train three times per week. All sessions will be supervised and remote. So that, each patient will connect with the physical exercise professional and with the other 4 participants by videocall. Moreover, the practitioner will monitor their heart rate in real-time because each patient will be given a MyZone heart rate (HR) control and platform access to MZ-Remote. In this way the professional will be able to adjust their workout intensity according to their HR, in the cardiovascular exercises and the weightlifting load in the resistance exercises; and to control and correct, participants’ posture and technique. Moreover, these measures will be determinant to asses participants’ exercise adherence. During the sessions, participants will be able to see their HR and HR of the rest of their training group. In addition, to promote social interaction an extra link will be given to those patients which want to see each other while practicing exercise. The necessary material to perform the exercise programs will be given to each participant in the before-intervention evaluation. This training kit will include a barbell of 2 kg, 2 weight discs of 5 kg, 2 weight discs of 2.5 kg, 2 weight discs of 1.25 kg and a Myzone's MZ-3 Belt chest strap.

Each session will last approximately 60 min and will include a warm-up, a main part composed of cardiovascular resistance exercises and a cooldown. The warm-up, lasting from 5 to 10 min, will include upper, lower body and truck mobility, and core muscular activation. The cooldown part will last about 5 min and will combine stretching of the muscles involved during the corresponding session. Moreover, during the stretches, breathing feedback will be given to fully relax and enhance elongation during the exhalation phase.

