### Outcomes

The following outcomes will be assessed in person by the oncology group at the hospital (Marqués de Valdecilla Hospital) or by a physical exercise professional at the sports center (GOfit) when it corresponds. The evaluations will be carried out before, after the intervention and 3 and 6 months after the end of the intervention to all the participants (HRVG, PEG and CG). To ensure CG measurements and follow up evaluations the principal investigator will call or write participants each month.

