#### Physical exercise evaluations

##### Cardiorespiratory fitness measurement

To record the cardiorespiratory capacity, maximum heart rate and the patients' perception of effort, the Bruce incremental submaximal test (modified) [73] will be performed on a treadmill. During the test, the patients will wear a Polar H10 chest strap to monitor their heart rate. Thus, following the protocol created by Bruce, the treadmill will start with a 0% incline and a speed of 1.7 m/h which will be maintained during the first 3 min. Every 3 min both the speed and the incline will be increased until the participants decide that their fatigue is too high to continue. In addition to constant heart rate monitoring to record the maximum heart rate, the patient will be asked about her perception of exertion every minute. By acquiring the maximum heart rate we can then prescribe the target intensity from the reserve heart rate using Karvonen's formula [74]. At the end of the test, the recovery heart rate will be recorded 1 min after stopping the test in order to assess the recovery rate. Subsequently, the maximum oxygen consumption of each patient (VO_2max_ = 2.282* (time) + 8.545) will be calculated from the formula proposed by the creators. This submaximal test has been commonly used in cancer patients in different exercise interventions [75].

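### Randomisation precedes baseline testing and no withholding of the arm is described, so effort-dependent and self-reported baselines, and the group × time estimates built on them, are open to bias

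*Protocol article*

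**What the plan says.** Under Randomization and allocation, the protocol article sets the order of events: "Before baseline assessments, participants are randomly assigned to one of the three groups". The same section says "The study is a blinded, randomized, controlled trial" and does not say who is blinded.

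Other sections bear on what is known and measured at baseline:

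- **Recruitment and eligibility.** Patients are called in "to explain in detail the study and each intervention group requirement".
- **Physical exercise programs.** "The necessary material to perform the exercise programs will be given to each participant in the before-intervention evaluation".
- **Outcomes.** Assessments are done by the hospital oncology group "or by a physical exercise professional at the sports center (GOfit) when it corresponds". No masking of either is described.
- **Cardiorespiratory fitness measurement.** The treadmill test runs "until the participants decide that their fatigue is too high to continue", and VO2max is then computed from the test time. The same test feeds the training prescription: "By acquiring the maximum heart rate we can then prescribe the target intensity from the reserve heart rate".
- **Psychosocial outcomes.** These come from self-administered questionnaires.
- **Statistical analysis.** Repeated-measures ANOVA, or Kruskal–Wallis, is planned with group and time as factors. The pre-intervention measurement is one level of time, and group × time is reported for each dependent variable.

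**The concern.** A baseline is safe to use in a change or group × time analysis when it cannot have been affected by the allocation. Collecting it before allocation, or before anyone involved knows the allocation, guarantees this. Here the stated order removes the first safeguard, and the text describes nothing that would supply the second.

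The exposed measures are not marginal. Peak oxygen uptake is one of the two outcomes used for the sample size, and the trial's estimate of maximal uptake depends on when the patient chooses to stop. Strength, jump and chair-stand results depend on effort. The psychosocial outcomes are self-reported. A patient who has just learned that she is in the control group, or in a demanding exercise group, may try harder, try less or answer differently. An assessor who knows the arm may encourage differently.

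Baseline maximum heart rate and repetition maximum also set the training load. A shift there could therefore alter the delivered intervention as well as the estimate.

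**Working it through.** The plan gives no figure on this point, so there is nothing to reproduce. The check has three steps.

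**1. Is the arm likely to be known at baseline?** Assignment comes before baseline (Randomization and allocation). The requirements of each group are explained at enrolment (Recruitment and eligibility). Exercise material is given out at the pre-intervention evaluation (Physical exercise programs). No section delays disclosure or masks the assessor. Knowledge of the arm is a well-supported inference, but the article does not state it.

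**2. How does a baseline shift travel through the analysis?** Suppose there is no true effect and one arm's mean baseline is lowered by b (in baseline SDs) because the arm is known, with no such shift later. Let ρ be the correlation between baseline and post-intervention values.

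- Difference in change (group × time): bias = b; SD of change = √(2(1 − ρ)).
- Difference adjusted for the shifted baseline: bias = ρb; residual SD = √(1 − ρ²).
- Post-intervention difference only: bias from this source = 0.

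The documents give neither b nor ρ, so both are assumptions. I take n = 25 per arm from the strain calculation under Sample size. I also take n = 30, which is 90/3 and assumes equal allocation. Tests are two-sided at 5%, by normal approximation.

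Example with n = 25, ρ = 0.7, b = 0.2: the SD of change is √0.6 = 0.775 and the standard error is 0.775 × √(2/25) = 0.219. The standardised shift is 0.2/0.219 = 0.913. The false-positive rate is P(Z > 1.96 − 0.913) + P(Z < −1.96 − 0.913) = 0.148 + 0.002 = 15.0%.

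| Assumed b | Bias in change | False-positive rate (n = 25, ρ = 0.7) |
|---|---|---|
| 0 | 0 | 5% |
| 0.1 SD | 0.1 SD | 7.4% |
| 0.2 SD | 0.2 SD | 15.0% |
| 0.3 SD | 0.3 SD | 27.8% |

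At b = 0.2 the rate runs from 10.9% (ρ = 0.5) to 20.1% (ρ = 0.8) with n = 25, and from 12.1% to 23.2% with n = 30. Adjusting for the affected baseline helps only in part: at b = 0.2 and ρ = 0.7 the bias is 0.7 × 0.2 = 0.14 SD, and the rate is 10.7% with n = 25.

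**3. The same in the plan's own units.** The plan's formula is VO2max = 2.282 × time + 8.545. The unit of time is not given; I assume minutes. A 30-second shift in one arm's mean at baseline, absent later, gives 2.282 × 0.5 = 1.14 units of spurious difference in change. One patient stopping early does not do this; the arm mean has to move.

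**The case against.** The strongest reply is that the article gives the time of assignment, not the time of disclosure. Explaining each group's requirements is not the same as telling a patient her group. The kit could be handed over after the tests, and it is common to both exercise arms, so it does not separate them. The timeline figure and the SPIRIT file are not shown and may add detail. This stands as far as it goes: knowledge of the arm is likely, not proven. It does not answer the fact that the stated order makes a safeguard necessary and the text describes none.

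Some stronger readings are tempting, but the documents do not support them:

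- **That every change and group × time estimate is biased.** Troponin, NT-proBNP, lipids, glucose and echocardiographic ejection fraction and strain depend on neither effort nor self-report. Strain is the outcome with the larger sample-size requirement.
- **That the bias favours exercise.** Disappointed controls who try less at baseline would later show inflated gains, which works against exercise. Other reactions work the other way.
- **That disqualifying injuries surface only after randomisation.** The exclusion of patients where "they have any injury which prevents them to perform the intervention or the evaluation correctly" belongs to the first enrolment phase. A missed injury could still appear later, but the text does not place this check at baseline testing.
- **That patients are lost between randomisation and baseline.** No section reports or implies such losses.
- **That nobody can be blinded.** Patients and trainers cannot be blinded to exercise versus usual care. Assessors, laboratory staff or the analyst could be.
- **That the bias is a known share of the detectable difference.** The article gives no effect size or SD from which to compute one.

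**Conclusion.** The point holds as a risk of bias, confined to effort-dependent, self-reported and assessor-dependent outcomes: treadmill time and VO2max, strength and jump tests, and questionnaires. For these, any arm-related baseline shift that is absent later passes in full into the change and group × time estimates, and baseline adjustment removes only part of it.

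The actual size and direction are unknown. The 1.14 VO2max units and the false-positive rates above show the mechanism under assumed shifts and correlations; they are not estimates for this trial. The conclusion rests on the stated order, on the absence of any described withholding of the arm, and on the inference that the arm is likely to be known at baseline. The unqualified claim of blinding needs correcting in any case, because it cannot apply to patients and trainers for exercise versus usual care.

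**What to change.** **Patients still to enrol.** Recruitment is under way and is planned over 24 months, so a change can still help. Complete the baseline tests, the questionnaires and the baseline HRV week before allocation is made, or at least before it is disclosed to patient and assessor. Hand over the kit afterwards. If this is done, the shift from this source is zero by construction.

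**Patients already randomised.** Record for each whether the patient and the assessor knew the arm at baseline. Run a sensitivity analysis by order of baseline and allocation. If few patients have baseline first, it will be imprecise and should be reported as such. Add a post-intervention between-group comparison that does not use the post-allocation baseline; the independent-samples tests already planned may supply it. That comparison is free of baseline contamination, but not of arm-related effort or reporting at the later visit.

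**Wording.** Replace the unqualified term with a list of the roles that are blinded, and state that patients and trainers are not blinded to exercise versus usual care.

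**Cost.** A short protocol amendment with the matching registry update, a reordering of steps, and a later hand-over of the kit. No extra measurements on patients are needed. Baselines already taken after allocation cannot be recovered, so the change is worth making early.

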#### Ethical approval and registration

The design of this study complies with the Helsinki Declaration of 2014. Moreover, the ethical standards of the study have been approved by the ethical committee of the Rey Juan Carlos University (approval number: 1901202103121) and the ethical committee of the University Hospital of Marqués de Valdecilla, named Valdecilla Health Research Institute (IDIVAL) (register identification number: 42//2021). Both, the study registration and the positive ethics committee approval were carried out before the recruitment. Besides, all the participants are informed about the relevant aspects of this study before starting their program including the potential benefits and risks of practicing exercise. Any change in the protocol will be expressed on the clinical registration website of ClinicalTrials.gov.

#### Sample size

Given that, to our knowledge, no previous studies have examined the effects of an exercise program guided by daily HRV in breast cancer patients and its comparison to a moderate to high-intensity exercise group and a control group, the sample size was calculated by considering the exercise intensity differences between groups. In this regard, we have taken as reference values interventions carried out with three groups, a high-intensity group, a moderate-intensity group and a control group. Moreover, the oxygen consumption peak (VO_2peak_) has been selected to make the calculations due to its importance in cardiovascular and physical health. The chosen tool to analyze sample size has been using G-Power 3.1 and the calculation were done basing us on the data from the investigations carried out by Martin, Battaglini [46] and Northey, Pumpa [47] two different studies. In both cases, between-group significant differences were reported.

A total of 18 patients, (11 allocated to the experimental and 11 allocated to the control group) would be needed in the worst of the cases to achieve a 99% statistical power for VO_2peak_. Moreover, regarding the low number of participants obtain, the calculations concerning the effects of exercise in Global Longitudinal Strain (GLS) compared to a control group were also done. In this case, the data employed for the calculation was from Costello, Roberts [48] where significant differences within and between groups were achieved. So, in the prior calculations performed, we would need a total of 50 patients [25 in each group] to achieve a 99% statistical power (two tails). Therefore, assuming 20% of dropouts, 90 patients will be recruited and allocated to one group or the other. Due to the large number of patients that are estimable to be enrolled in the study, the recruitment and intervention will be carried out progressively over 24 months depending on the number of patients to be recruited.

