**Methods:**

For this purpose, a 16-week intervention will be carried out with 90 breast cancer patients distributed in 3 groups (a control group, a moderate to high-intensity preplanned exercise group and a high-intensity exercise group guided by HRV). Both physical exercise interventions will be developed remotely and supervised including strength and cardiovascular exercises. Physiological variables, such as cardiotoxicity, biomarkers, lipid profile, glucose, heart rate and blood pressure; physical measures like cardiorespiratory capacity, strength, flexibility, agility, balance and body composition; and psychosocial variables, as health-related quality of life, fatigue, functionality, self-esteem, movement fear, physical exercise level, anxiety and depression will be measure before, after the intervention and 3 and 6 months follow up.

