### Aim and research questions

Therefore, given the potential benefits of physical exercise and the possibilities of optimizing how it is prescribed for cancer patients, the current randomized controlled trial aims to analyze the effectiveness of a high-intensity remote exercise program guided daily by HRV compared to a pre-planned remote moderate to high-intensity exercise program in breast cancer survivors. For this purpose, the effects of both physical exercise programs on physiological (cardiotoxicity, inflammatory factors, cardiovascular variables, body composition and anthropometric parameters), physical (low and upper body strength, cardiorespiratory fitness, low and upper body flexibility, agility and balance) and psychological health (HRQoL, fatigue, life satisfaction, self-esteem, anxiety and depression, shoulder disability perception, physical activity, kinesophobia and exercise motivation) measurements of breast cancer patients will be assessed and compared an inactive control group.

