Moreover, as it has been developed before in athletes [39], but not in clinical populations, the intensity of HRVG participants will be adjusted according to rMSSD values, as a reflection of the parasympathetic activity. rMSSD suffers normally a decrease during and after cancer treatments [121, 122], which exercise may regain by a decrease of renin and angiotensin, affecting the renin–angiotensin–aldosterone system; a decline of oxidative stress and inflammation caused by the increase in catecholamines impacting, therefore, in tumour cell microenvironment by an exponential decrease of reactive oxidative species and an increment in antioxidants [61, 123–126]. In this way, to get an rMSSD increase and adapt to their training load to their physiological stress, if patients' rMSSD goes beyond their individual limits, they will not perform in those days high-intensity and will follow PEG intensity until their values return to their corresponding normality [127]. This novelty way to prescribe and adapt high-intensity exercise to patients daily could provide a new tool to reach higher benefits. Two recent meta-analyses have stated that high-intensity exercise does not produce higher positive changes in the VO_2max_ [23] and HRQoL [26] of cancer patients than moderate intensity. In this regard, we hypothesize that maybe not all patients reacted equally to high-intensity, and they need more individualization concerning their disease's long-term side effects, especially the related cardiovascular abnormalities.

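### The reported 99% power covers exercise versus control, not HRVG versus PEG, and the sample-size figures do not agree with each other

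*Protocol article*

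**What the plan says.** The abstract describes "90 breast cancer patients distributed in 3 groups": control, pre-planned exercise (PEG) and HRV-guided exercise (HRVG). The Aim and research questions section sets out to analyse "the effectiveness of a high-intensity remote exercise program guided daily by HRV compared to a pre-planned remote moderate to high-intensity exercise program", and its next sentence adds comparison with an inactive control group.

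The Sample size section gives its basis as follows: "the sample size was calculated by considering the exercise intensity differences between groups". It names three-group studies (high intensity, moderate intensity, control) as its reference. It then reports two results:

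- **VO2peak**, 99% power, least favourable case: "A total of 18 patients, (11 allocated to the experimental and 11 allocated to the control group) would be needed".
- **Global longitudinal strain (GLS)**, exercise compared with control: "we would need a total of 50 patients [25 in each group] to achieve a 99% statistical power (two tails").

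It concludes: "Therefore, assuming 20% of dropouts, 90 patients will be recruited and allocated to one group or the other". No effect size, SD, alpha, test family or allocation ratio is given. The Statistical analysis section plans a Bonferroni adjustment without naming the family of tests.

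**The concern.** Two things are wrong on the face of the section. First, the numbers do not agree: a total does not equal its parts, and the recruited number, after the dropout that the section itself assumes, falls just short of the stated requirement. Second, the stated basis (differences in exercise intensity) and the reported calculations (an exercised group against control) answer different questions.

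The second matters more. HRVG versus PEG compares two exercising groups, and under the protocol HRVG trains at PEG intensity on days when its HRV falls outside the individual limits. The Discussion also cites two meta-analyses, on VO2max and on quality of life, that "have stated that high-intensity exercise does not produce higher positive changes" than moderate intensity. The difference between the exercise arms may therefore be well below that between exercise and control. Someone who sees 99% power beside an aim that names HRVG versus PEG will naturally join the two, and could then give a non-significant result on that comparison more weight than the design supports.

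**Working it through.** **Inputs from the Sample size section:** 11 and 11 with total 18; 25 per group, 50 in total, 99% power, two-sided; 20% dropout; 90 recruited. The abstract gives three groups.

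**Assumptions, because the article does not state them:** equal allocation; two-sided alpha 0.05, with 0.05/3 shown as one possible Bonferroni level (three pairwise tests); a two-sample t-test on a single continuous outcome.

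**1. VO2peak total.** 11 + 11 = 22, not 18. If 18 were right, the groups would be 9 each. Neither version drives the final size, because GLS needs 25 per group.

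**2. From 25 per group to 90.** The step is not shown, so possible routes were tried:

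- Two groups: 50 × 1.2 = 60, or 50 / 0.8 = 62.5, rounded up to 63. Neither gives 90.
- Three groups, multiplying: 25 × 3 × 1.2 = 90. This reproduces the stated figure.
- Three groups, dividing: 75 / 0.8 = 93.75, so 94 in total; or 25 / 0.8 = 31.25, so 32 per arm and 96 in total.

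The stated 90 therefore fits only inflation by multiplication. Working forward, 90 × 0.8 = 72, and 72 / 3 = 24 per arm, against 25 required.

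**3. What losing one patient per arm costs.** Power is P(|T| > t critical), where T is noncentral t with 2n − 2 degrees of freedom and noncentrality d × √(n/2).

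- Solving for 99% power at n = 25 and alpha 0.05 gives an implied d of about 1.24.
- At that d with n = 24, power is 98.7%; at alpha 0.05/3 it is 96.1%.

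For exercise versus control at the implied effect, neither the dropout slip nor a Bonferroni correction changes much.

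**4. HRVG versus PEG, 24 per arm.** The standardised differences are an assumed range, not trial figures.

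| True difference (SD) | Power, alpha 0.05 | Power, alpha 0.05/3 |
|---|---|---|
| 0.3 | 17% | 8% |
| 0.5 | 40% | 24% |
| 0.8 | 77% | 61% |

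- Smallest difference with 80% power: 0.83 SD at alpha 0.05; 0.96 SD at 0.05/3.
- Smallest difference with 99% power: 1.26 SD at alpha 0.05.
- Completers needed for 80% power at 0.5 SD: 64 per arm (86 at 0.05/3).

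**5. Sensitivity to the analysis.** With change scores and a pre–post correlation r, the detectable difference in baseline SD units is 0.83 × √(2(1 − r)). For r = 0.5 this is 0.83; for r = 0.8 it is 0.83 × 0.632 = 0.52. These correlations are assumptions. A change-score or baseline-adjusted analysis could thus detect a smaller difference than the simple t-test suggests.

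**The case against.** Several points count against a stronger statement of this concern.

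- **A reader might infer that no HRVG–PEG type of calculation was ever done.** The article does not show that. It refers to three-group reference studies and reports only the least favourable VO2peak case, so others were probably run. What can be said is that none is reported for this comparison, and that the stated basis and the reported results differ.
- **A reader might take HRVG versus PEG as the formally designated lead comparison.** No contrast is so designated. The abstract's primary objective covers all three groups, so exercise versus control is also within scope. HRVG versus PEG is nevertheless the comparison that the aim names first.
- **A reader might conclude that 99% is wrong, or that the dropout and Bonferroni points undermine the size.** Without effect size, SD and alpha, the 99% cannot be shown wrong for exercise versus control, and the two corrections leave 98.7% and 96.1% at the implied effect. The 0.05/3 level is itself an assumption.
- **A reader might call a null HRVG–PEG result uninformative.** That goes too far. With 24 per arm, the 95% interval half-width is about 2.013 × √(2/24) = 0.58 SD, which can exclude large differences. The article already promises Cohen's d with a 95% confidence interval.
- **The cited meta-analyses do not estimate HRV guidance.** They concern VO2max and quality of life, not GLS, and the authors cite them to argue for individualising intensity. They make a modest difference plausible and do no more.

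All five stand as limits on the claim. None removes the 18/22 error, the 24 against 25, or the absence of any reported power for a comparison named in the aim.

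**Conclusion.** The Sample size section needs correction. The total of 18 is inconsistent with 11 + 11. Under equal allocation, 90 patients with 20% dropout give 24 completers per arm, one below the stated 25; the effect on power is negligible. The substantive point is that the 99% figure belongs to experimental or exercise versus control and does not carry over to HRVG versus PEG, for which no power or detectable difference is reported.

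The size of that gap can only be illustrated. On a two-sample t-test with 24 per arm, 80% power needs about 0.83 SD (0.96 SD at 0.05/3), and power at 0.5 SD is about 40% (24%). These values rest on assumed alpha, allocation, Bonferroni family and analysis, and should not be printed as facts about the trial.

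**What to change.** Keep 90 patients and revise the text:

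1. Correct the VO2peak figures so that the total and the group sizes agree.
2. Show the step from 25 per group to 90, and state that about 24 per arm are expected to complete (with the allocation ratio).
3. Limit the 99% power statement to exercise versus control.
4. State the effect size, SD, alpha and Bonferroni family that the sponsor actually used, and from these report the HRVG–PEG difference detectable under the planned analysis. The figures above are a check on scale and not a substitute for the sponsor's own.
5. State that a non-significant HRVG–PEG result will be read from its estimate and confidence interval, and not as evidence of equal effect.

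The cost is wording and one recalculation, with no extra patients. The downside is that the stated power will look less favourable.
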